### Study design, registration, and ethics

The study protocol was conducted according to the Declaration of Helsinki and approved by the local ethical committee of our hospital (S-454/2017). Furthermore, it was registered at the German Clinical Trials Register (DRKS00013562).

This study is a registered, clinical, prospective, randomized, controlled, single-center, two-arm, parallel group trial with a 1-year follow-up, carried out at a level 1 trauma center.

### Inclusion and exclusion criteria

Patients older than 18 years who suffer from acute syndesmosis rupture, both isolated and in combination with fractures of the lateral malleolus (Weber C and Maisonneuve fractures) and who are undergoing surgery within 8 days for a syndesmotic rupture at our Center for Orthopedics and Trauma Surgery will be included in this study after giving their informed consent.

Exclusion criteria are pregnancy, the disability for approval, congenital deformities of the lower extremities, missing informed consent, and refusal of participation. Patients with any known contraindications for MRI examination will be excluded as well.

### Study setting and population

Study patients pass a follow-up over 1 year with clinical and radiologic examinations 1 day before and after the initial operation as well as 6, 12, 26, and 52 weeks after treatment in our outpatient clinic. In this study, there is no need for additional clinical examinations for the patients, with the exception of an additional motion analysis and a MRI 6 months after initial treatment to evaluate the biomechanical outcome and the healing status of the syndesmosis ligament.

Surgery and examinations will be performed by an experienced orthopedic and trauma surgery consultant.

The patients will be randomized to the different treatment options (screw fixation or TightRope®).

The following questionnaires will be used for clinical and psychosocial evaluation:
“Study questionnaire screw vs. TightRope”.“SF-12 – Health survey” [19].“Score of Olerud und Molander (OMAS)” [20].“Pain on a VAS”.“Foot and ankle outcome score (FAOS)” [21].

In the following, the procedure of this study is described and additionally illustrated in Fig. 1Diagnosis of an acute syndesmosis rupture (isolated or combined) and indication of surgical treatment in our clinic.Informed consent and inclusion.Randomization 1:1 to the different treatment options (screw fixation or TightRope®).Preoperative clinical and radiologic examinations.Preoperative clinical and psychosocial evaluations with questionnaires abovementioned.Surgery with screw fixation or TightRope®.Standardized intraoperative CT/3D imaging with ISO C 3D or CIOS Spin (Siemens Healthineers GmbH, Erlangen, Germany) for assessment of syndesmosis reduction.Postoperative clinical and radiologic examinations with X-ray of foot and ankle.Clinical and radiologic follow-up (6 weeks, 3, 6, 12 months) postoperatively + abovementioned questionnaires.Additional standard clinical instrumented 3D gait analysis to evaluate the biomechanical outcome (duration: 30 min) 6 months after the operation.Additional MRI of the ankle joint to evaluate the healing status of the syndesmosis ligament (duration 30 min) 6 months after the operation.

**Fig. 1 Fig1:**
[figure not shown]
Flowchart of the study protocol

**Fig. 2 Fig2:**
[figure not shown]
Study process schedule (according to the Standard Protocol Items: Recommendations for Interventional Trials (SPIRIT) guidelines)

### Participants and consent

All patients assigned for surgical treatment of acute syndesmosis rupture at our level 1 trauma center can be involved in our study. Patients must be at least 18 years of age without any exclusion criteria and provide their written consent before any study-relevant intervention. Before participation, each patient, suitable to the study protocol, will be fully informed by informed consent about the scientific purpose and risks associated with the procedures. The participation is voluntary and every participant is able to withdraw their consent to participate in the trial at any time without giving reasons.

Informed consent takes place in a one-to-one appointment at a trauma center with an experienced orthopedic and trauma surgeon. A full verbal explanation of the study, a written patient information sheet, and informed consent form will be provided before inclusion*.*

### Randomization

Patients will be randomly assigned to one of two groups (intervention or control) using a computer-generated random block assignment in a 1:1 ratio using nQuery Advisor v7.0 software (Statsols, Cork, Ireland). This method helps in maintaining the balance of treatment assignment while reducing the potential for selection bias. Patients, researchers performing the follow-up examination, and the trial statistician will be blinded to the group allocation. If the treatment of syndesmosis rupture is not accomplished after randomization due to an intraoperatively observed missing acute syndesmosis rupture with no need of stabilization, the patient will be excluded from final analysis. At the date of screw removal 6 to 8 weeks after the operation, a blinding of the patients will no longer be possible.

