## Study design/methods

### Objectives and hypotheses

The objective of this prospective randomized controlled single-center study is the comparison of gait analysis, clinical and radiographic outcome after stabilization of an acute syndesmosis rupture with either a static implant (a 3.5-mm metallic screw through three cortices) or a dynamic device (TightRope®). Due to the pilot study design, further objective is to generate additional possible hypotheses.

The following hypotheses will be tested:
H0: The biomechanical (regarding ankle range of motion and maximum plantar flexion power in the gait analysis), clinical (study questionnaire, SF-12, OMAS, VAS, FAOS), and radiological outcome is different in both treatment options.H1: The biomechanical (regarding ankle range of motion and maximum plantar flexion power in the gait analysis), clinical (study questionnaire, SF-12, OMAS, VAS, FAOS), and radiological outcome is equal in both treatment options.

Patients with acute syndesmosis rupture (isolated or combined), suitable according to the study protocol, will be randomized to the two different treatment options (screw fixation or TightRope®).

Syndesmosis reduction will be assessed using CT/3D imaging intraoperatively with ISO C 3D or CIOS Spin (Siemens Healthineers GmbH, Erlangen, Germany) as a part of our standard procedure.

Six months after the initial treatment, the patients will receive an additional gait analysis and a MRI in the follow-up examination at our outpatient clinic

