### Surgical treatment

The fractures will be fixed within 8 days of the initial trauma in both groups using standard AO (Arbeitsgemeinschaft für Osteosynthesefragen) [22] principles. Antibiotic prophylaxis will be given perioperatively. Open reduction and internal fixation (ORIF) of fibula fractures will be treated either with a 1/3 tubular plate with or without lag screws or in high fibula fractures with syndesmosis fixation only. Additional fractures of medial and/or posterior malleolus will be treated according to standard principles before stabilizing the syndesmosis. The distal tibiofibular joint will be reduced without direct visualization of the syndesmosis and held at its anatomical position by a reduction clamp. The ankle joint will be positioned at an angle of 90° between the tibial shaft and the foot during syndesmosis fixation in accordance with the randomization (cortical screw or TightRope®).

For the static syndesmotic screw fixation, a 2.5-mm hole will be drilled under fluoroscopic guidance, approximately 2 cm above and parallel to the distal tibial joint line from lateral to medial. If plating of the fibular fracture is necessary, the hole will be drilled through an empty screw hole. Three cortices will be drilled through and a 3.5-mm screw will be tightened.

For the dynamic fixation of the syndesmosis by means of TightRope®, a 3.5-mm hole will be drilled under fluoroscopic guidance, approximately 2 cm above and parallel to the distal tibial joint line (through a hole of the plate if present) from lateral to medial. A guide needle will be inserted from lateral to medial through the drill hole to position the oblong button over the medial tibial cortex and confirmed by X-ray. Afterwards, the assembly will be tensioned by pulling the free ends of the FiberWire on the lateral side. These will be hand-tied with a surgical knot and the round button will be firmly applied on the lateral cortex of the fibula (or onto the plate if present). After achieving an adequate syndesmotic fixation by either technique, the reduction clamp will be removed and the stability controlled under fluoroscopy.

After syndesmosis fixation, intraoperative CT/3D imaging with ISO C 3D or CIOS Spin (Siemens Healthineers GmbH, Deutschland) will be performed to evaluate syndesmosis reduction.

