The postoperative treatment protocol is similar in both groups. The ankle will be immobilized in a below-the-knee cast with the ankle joint at 90° for 6 weeks with partial weight-bearing. Between the 6th and 8th week, only the static syndesmosis screw will be removed in a standardized outpatient surgery. The dynamic fixation of the syndesmosis by means of TightRope® needs no removal postoperatively. Afterwards, weight-bearing can be gradually increased with approximately 20 kg per week until full weight-bearing is achieved.

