### Follow-up

Subsequent to surgery, all patients will receive similar follow-up procedures. Follow-up at our trauma center is standardized, based on a well-established protocol, and all procedures and diagnostics are based solely on medical indications. First radiological and clinical evaluation of the surgical treatment will be performed on day 2 after surgery. Discharge from hospital will be realized as soon as general health conditions (soft tissue conditions, patient mobility and pain level) allow it. Afterwards, patients will receive physiotherapy and manual lymphatic drainage. Further clinical and radiographic evaluations are planned for 6 weeks and 3, 6, and 12 months after surgery following our standardized procedure for fracture patients treated in our hospital (Table 1). There are no additional follow-up appointments or X-ray examinations necessary for the study. Merely the gait analysis and MRI control of the syndesmosis will be performed 6 months postoperatively during the regular follow-up appointment.

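### Follow-up examiners are declared blinded without limit, although the scheduled imaging reveals the arm to any examiner who views it and to the reader of the primary MRI

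*Protocol article*

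**What the plan says.** The blinding statement stands in the protocol article under Randomization: "Patients, researchers performing the follow-up examination, and the trial statistician will be blinded to the group allocation". It sets no time limit and makes no exception for examiners. The same section then concedes one loss: "At the date of screw removal 6 to 8 weeks after the operation, a blinding of the patients will no longer be possible".

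Imaging accompanies the clinical visits. Study setting and population plans "clinical and radiologic examinations 1 day before and after the initial operation as well as 6, 12, 26, and 52 weeks after treatment". Follow-up repeats this: "Further clinical and radiographic evaluations are planned for 6 weeks and 3, 6, and 12 months after surgery".

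The arms differ in what stays in the ankle. Under Surgical treatment, between weeks 6 and 8 "only the static syndesmosis screw will be removed in a standardized outpatient surgery"; the TightRope needs no removal.

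The first-listed primary endpoint (Primary outcome measures) is healing of the syndesmosis on MRI at 6 months, classified by a senior radiologist. Gait analysis at 6 months is the other primary measure.

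On staff roles, Study setting and population says "Surgery and examinations will be performed by an experienced orthopedic and trauma surgery consultant". The sample size section instead lists the surgeon and the doctor responsible for examinations and questionnaires as separate parties.

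**The concern.** A blinding statement is a design property that readers rely on when they judge a comparative result. Here it covers follow-up examiners through 12 months, while the article's own imaging schedule and implant handling give away the allocation to anyone who looks at the films. The concession for patients makes this more misleading: by naming one loss of blinding, the section implies that there is no other.

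What is at stake is mainly the MRI endpoint. It is one reader's classification of whether the appearances are normal, and the section gives no numerical threshold for it. A judgement of that kind is open to expectation, and the article states its expectation in the Abstract, Background and Discussion: dynamic fixation is to be equivalent or better. If the final report repeats the sentence as it stands, it will claim protection that these readings did not have.

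**Working it through.** No arithmetic applies. The question is whether the blinding sentence agrees with the rest of the article.

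1. **Who is said to be blinded.** Patients, follow-up examiners and the statistician (Randomization). The time limit applies to patients only.

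2. **When images are taken.** At 6 weeks and at 3, 6 and 12 months, together with the clinical evaluation (Study setting and population; Follow-up). That is all four follow-up visits after discharge.

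3. **Whether the implants can be seen.** The screw is described as metallic (Objectives and hypotheses). For the TightRope, a guide needle serves to "position the oblong button over the medial tibial cortex and confirmed by X-ray". Both devices are therefore visible on plain films, and they differ in form.

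4. **What is in the ankle at each visit.**

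| Visit | Screw arm | TightRope arm | Arm identifiable from the film? |
|---|---|---|---|
| 6 weeks | Screw, unless just removed | Buttons | Yes, by form or absence of the device |
| 3 months | No syndesmotic screw | Buttons | Yes, by presence or absence |
| 6 months (also MRI) | No syndesmotic screw | Buttons | Yes, by presence or absence |
| 12 months | No syndesmotic screw | Buttons | Yes, by presence or absence |

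5. **The MRI reader.** The MRI is taken at 6 months, at least 4 months after the end of the removal window, and is read in the region that the retained device crosses. The article does not itself say that the device shows on MRI; I take that as a reasonable inference. The blinding sentence does not name the radiologist. If the radiologist counts as a follow-up researcher, the sentence does not hold for the primary endpoint. If not, the primary endpoint has no stated blinding. Either way the text needs an explicit statement.

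6. **Staff roles.** One section gives surgery and examinations to a consultant; another separates the surgeon from the examining doctor. Only the second arrangement is plainly compatible with blinded examiners, so the two should be made to agree. Steps 2 to 5 do not depend on this.

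7. **Who could remain blinded.** The statistician; patients until screw removal, as already stated; and staff who see neither images nor operation notes, for example those who process the gait recordings.

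**The case against.** The strongest reply is that the article never says the blinded examiner looks at the images. Film review may be separated from the clinical examination, and a condensed article can leave that to the full protocol. This stands in part: it is why the point is confined to examiners who view images and does not say that assessor blinding is impossible. It does not rescue the unqualified sentence, which the schedule in the same article contradicts for anyone who does view them.

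Four stronger readings are tempting and are not supported.

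- A reader might infer that after weeks 6 to 8 only one arm contains metal. Surgical treatment provides for fibular plates, lag screws and fixation of other malleolar fractures irrespective of arm. Only the syndesmotic device distinguishes the arms.
- A reader might infer that the operating surgeon examines his or her own patients. The sentence on surgery and examinations names a grade of staff, not one person, and the sample size section points the other way.
- A reader might infer that the unblinding behind the questionnaires at 3, 6 and 12 months is concealed. It is disclosed for patients in the Randomization section.
- A reader might wish to put a number on the bias. The documents give neither an expected healing rate nor any data on reader bias, so a figure would rest on invented inputs.

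It might also be argued that the comparison should rest on gait instead of MRI. That does not follow. Patients walk at self-selected speed (Background) and by 6 months may know whether they had a second operation, so masked processing of the recordings does not make the gait outcome itself masked.

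**Conclusion.** The concern holds in a limited form. The article claims blinded follow-up examiners without qualification, and its own schedule does not deliver this for any examiner who views the images. The reader of the 6-month MRI can likewise identify the arm, and the article does not say whether that reader is meant to be blinded.

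In extent, it touches the first-listed primary endpoint in all planned patients (25 + 25 = 50) and, where examiners see films, all four follow-up visits. Its effect on the estimated difference cannot be quantified from the documents.

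The conclusion assumes that the films taken at the visits are available to at least some examiners, and that a retained TightRope can be recognised on MRI. It does not depend on whether surgeon and examiner are the same person. The correction should be made before results are reported; it does not undermine the design or the choice of endpoints.

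**What to change.** Change the text:

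- In Randomization, limit the statement to the roles and assessments where it can hold: the statistician, patients until screw removal (as already written), and staff who do not see images.
- State that readers of X-rays and MRI, and any examiner who views images, are not blinded to the implant. Say expressly what applies to the senior radiologist.
- Reconcile Study setting and population with the sample size section on who operates and who examines.

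Protect what can be protected with existing staff:

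- Derive ankle range of motion and maximum ankle power from pseudonymised gait files, without access to imaging or operation notes. The article already stores data under pseudonyms.
- Have questionnaires completed before the examination and imaging at each visit. This does not restore blinding after screw removal, but it keeps image findings and examiners' remarks out of the answers.
- Withhold clinical and gait results from the radiologist.

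In the report, keep the MRI endpoint as a primary outcome and describe it as read with the arm identifiable. Note that patients are no longer blinded at the gait test.

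The cost is wording and the order of steps within visits that already take place. No extra visit, assessor or patient is needed, and treatment is unchanged. The downside is a weaker blinding claim in the report.

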### Sample size calculation and statistical analyses

Formal sample size determination is not possible as potential effects are not yet known. Data from previous studies were utilized to determine the necessary sample size [23–25]. We plan a sample size of 25 patients, who will be treated with the cortical screw fixation and 25 patients, who will be treated with the dynamic TightRope® system within 2 years. The patients will be randomized to the two different treatment options. The randomization will be independent of the surgeon and the doctor who will do the examinations and the questionnaires.

The Shapiro-Wilk test will be used to check if our population is normally distributed. Standard unpaired Student’s *t* test to detect significant changes between the two groups will be conducted, if they are normally distributed. In contrast, possible differences for continuous data and scores between groups will be evaluated with the Wilcoxon *U* test, if no normal distribution exists.

The empirical distribution of continuous data and scores will be reported and calculated with means, standard deviation (SD), median, minimum, and maximum values and with absolute and relative frequencies for categoric data as well as unpaired *t*-test *p* values to depict a significant difference between the different groups. All descriptive analyses will be calculated for demographic data and for the dependent variables derived from the functional assessment, gait analyses results, and questionnaires of both groups.

An independent senior statistician of the Institute of Medical Biometry and Informatics of our university will perform the analysis. The intention-to-treat population will be used.

The analysis and illustrations will be carried out by use of SPSS version 25.0 for 135 Windows (IBM Corp., Armonk, New York, USA) and GraphPad Prism version 6.00 for Windows (GraphPad Software, San Diego, California, USA). For the representation of statistical relationships, the Pearson correlation coefficient will be used. The final details of the statistical analysis will be established in a statistical analysis plan, which will be completed before the closing of the database (before the end of data collection). A *p* value of ≤ .05 will be used to indicate statistical significance. Only a complete follow-up examination will be considered in the statistical analyses.

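### Excluding randomised patients on a finding made during surgery contradicts the stated intention-to-treat analysis, and no stated safeguard keeps that exclusion independent of arm

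*Protocol article*

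**What the plan says.** Four statements in the protocol article bear on this.

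- **Order of events.** The numbered procedure under Study setting and population puts allocation after consent and ahead of both the baseline assessments and surgery: "Randomization 1:1 to the different treatment options (screw fixation or TightRope®).Preoperative clinical and radiologic examinations".
- **Exclusion rule.** The Randomization section covers the patient who is randomised but not treated because of an "intraoperatively observed missing acute syndesmosis rupture with no need of stabilization, the patient will be excluded from final analysis".
- **Analysis set.** Sample size calculation and statistical analyses states: "The intention-to-treat population will be used". It defines no modified set and makes no exception. The same section separately limits the analysis to patients whose follow-up is complete.
- **Blinding.** The Randomization section says: "Patients, researchers performing the follow-up examination, and the trial statistician will be blinded to the group allocation". The operating surgeon is not in that list. Under Surgical treatment, the implant is placed "during syndesmosis fixation in accordance with the randomization (cortical screw or TightRope", so the surgeon knows the arm at that step at the latest.

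**The concern.** A patient who is randomised and then removed for something seen at operation is not in an intention-to-treat population. The article thus fixes two incompatible rules for who is analysed. This is more than detail left to a later analysis plan, because both rules are stated as settled.

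The exclusion would do little harm if it were decided without knowledge of the arm. The article states nothing that ensures this. It does not withhold the allocation until the need for fixation is recorded, and it does not have the decision reviewed by someone unaware of the arm. The arms also differ in what follows from fixation: under Surgical treatment, only the screw leads to a planned second operation for removal. If the arm were known, the threshold for declaring that no stabilisation is needed could differ between arms. Patients with a better prognosis would then leave one arm more often than the other, and a larger sample would not remove the resulting bias.

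A lesser consequence of the same ordering is that the preoperative questionnaires are completed after allocation.

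**Working it through.** **1. The contradiction.** This needs no figures. Allocation precedes surgery (Study setting and population). A finding at surgery removes an allocated patient from the final analysis (Randomization). The analysis is by intention-to-treat, unqualified (Sample size calculation and statistical analyses). The second and third statements cannot both hold for such a patient.

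**2. What the article gives for sizing the problem.** It gives 25 patients per arm, 1:1 allocation and a significance level of 0.05. It gives no exclusion rate, effect size, SD or healing rate, so everything below is illustration on assumed inputs.

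**3. Continuous outcome.** Let s be the share of mild ankles in each arm, with outcomes 1 SD better. Let e be the share of the arm excluded, all of them mild. With no true treatment effect, the mean of the analysed arm is raised by (s − e)/(1 − e) SD, and the bias is the difference between arms. Assume s = 0.20, which is 5 of 25.

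- 1 of 25 excluded against 4 of 25: (0.20 − 0.04)/0.96 − (0.20 − 0.16)/0.84 = 0.1667 − 0.0476 = 0.119 SD.
- None against 4 of 25: 0.2000 − 0.0476 = 0.152 SD.
- Equal exclusion in both arms: 0.

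For comparison, the 95% half-width with 25 per arm is t(48) × √(2/25) = 2.011 × 0.283 = 0.57 SD. With 24 against 21 analysed it is 2.017 × √(1/24 + 1/21) = 0.60 SD. The bias is roughly a fifth to a quarter of the half-width.

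**4. Healing outcome.** Suppose k of 25 ankles per arm are stable and all are rated healed, the rest heal with probability p, and only one arm excludes its stable ankles. The spurious difference is [k + (25 − k)p]/25 − p = k(1 − p)/25.

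| k | p = 0.8 | p = 0.6 |
|---|---|---|
| 1 | 0.8 points | 1.6 points |
| 3 | 2.4 points | 4.8 points |
| 5 | 4.0 points | 8.0 points |

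**5. The opposite problem: keeping everyone.** If k of 25 per arm have no rupture and no implant, and their outcomes do not depend on arm, a true difference D among treated patients becomes D × (25 − k)/25 in the full set. That is 0.88 D for k = 3 and 0.80 D for k = 5. Full inclusion therefore pulls the result towards equality, which Objectives and hypotheses sets as H1.

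**The case against.** The strongest reply is that the mechanism for bias is inferred. The article does not say when the surgeon learns the allocation. An allocation generated before surgery need not be disclosed before surgery; knowledge is certain only at implantation. If disclosure follows the check for rupture, the exclusion is blind to arm. An article may also leave such logistics to the full protocol, and its flowchart is not available here. This stands. A reader might infer that the surgeon could not be masked when deciding, or that exclusions do differ by arm; the text supports neither. The statement "The randomization will be independent of the surgeon and the doctor who will do the examinations and the questionnaires" does not settle it, because it concerns how the allocation is made and not who judges the exclusion.

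Three other tempting readings fail.

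- "The distal tibiofibular joint will be reduced without direct visualization of the syndesmosis" might be taken to show that the exclusion rests on unaided judgement. It describes how the joint is reduced before fixation, not how a rupture is confirmed or ruled out.
- It might seem that each excluded patient costs one of the 50 places. The article does not say whether such patients are replaced, and its 25 per arm can be read as treated patients.
- Baseline questionnaires after allocation might seem open to bias. Patients are stated to be blinded until screw removal, and the allocation is said to be independent of the doctor administering the questionnaires, so this is a minor point.

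It is also fair to object that keeping patients without a rupture in the main analysis is not plainly better. It dilutes differences when equality is the hypothesis to be shown, and healing of the syndesmosis is hard to define where nothing was torn. A declared modified intention-to-treat set is a legitimate alternative if the exclusion is made blind to arm. None of these replies removes the conflict between the exclusion rule and the stated analysis set.

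**Conclusion.** The point holds as a contradiction about who is analysed, together with a missing safeguard. The contradiction is explicit and rests on no assumption. Exclusion that depends on arm is permitted by what is written but is not demonstrated.

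Its size cannot be derived from the article. The figures of 0.12 to 0.15 SD, and of 0.8 to 8.0 percentage points in healing, assume particular shares of mild or stable ankles, a prognostic advantage for them, and markedly unequal exclusion. They show that the effect could matter in a trial of 50, not that it will. If the rule acts equally in both arms, the bias in these illustrations is zero.

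A reader might conclude that moving the allocation alone restores intention-to-treat. It does not, because the restriction to complete follow-up is a separate departure from it.

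**What to change.** 1. **Study setting and population; Randomization.** Complete the preoperative examinations and questionnaires first. Randomise, or disclose the concealed allocation, only after the surgeon has recorded in theatre that syndesmotic fixation is needed. This exclusion then no longer occurs after allocation. No treatment or clinical criterion changes.
2. **Patients already randomised.** Report these exclusions by arm, with whether the allocation was known when each decision was made. Present results both for all randomised patients as assigned and for a declared modified intention-to-treat set. Note that including ankles without a rupture dilutes differences towards equality.
3. **Sample size calculation and statistical analyses.** Name the resulting set correctly, and reconcile the rule that only complete follow-up is analysed with intention-to-treat.

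**Cost.** Allocation must be accessible in theatre with both implants on hand, so the implant cannot be laid out in advance. Trial status gives recruitment from December 2017 with completion expected in December 2019. A change during recruitment leaves the trial with two allocation procedures, which should be reported. If recruitment has already closed, only items 2 and 3 apply, and they cost little beyond definition and reporting.
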